##### Social and familiar functioning

2.3.1.4

- The Family Environmental Scale (FES) (Moos et al., 1974; Fernández-Ballesteros and Sierra, 1989). This questionnaire assesses interpersonal relationships between family members. For this study we use the dimension of family interpersonal relations, composed of 30 items with a true or false response format that measures three dimensions: cohesion (e.g., “In my family, there is a strong feeling of union”), expressiveness (e.g., “At home, we talk openly about whatever we want to discuss”) and conflict (e.g., “Our family members are in conflict with each other”). The Cronbach’s alphas for each dimension are 0.85, 0.80, and 0.86, respectively.-The Satisfaction With Life Scale (SWLS) (Diener et al., 1985; Pons et al., 2000; Muñoz de Arenillas et al., 2010) is a 5-item instrument that assesses the respondent’s degree of satisfaction with their life. The Cronbach’s alpha obtained in the Spanish version is of 0.83.- The Global Assessment of Functioning (GAF) (Endicott, 1976). This scale measures patients’ general functioning. Clinical and social functioning measures will be included. The validated Spanish version of the DSM-IV was used (American Psychiatric Association, 1996).

##### Protective factors

2.3.1.5

- The Rosenberg Self-Esteem Scale (RSES) (Martín-Albo et al., 2007) explores through 10 items personal self-esteem understood as feelings of personal worth and self-respect. Cronbach’s alpha for the Spanish version was 0.85.- The Connor-Davidson Resilience Scale (CD-RISC 10) (Connor and Davidson, 2003; Notario-Pacheco et al., 2011). The 10-item scales assess resilience through three dimensions: self-efficacy-tenacity, personal control and social competence. Cronbach’s alfa for the Spanish version was 0.81.- The Coping Strategies Inventory (CSI-SF) (Tobin et al., 1989; Cano-García et al., 2007; Tous-Pallarés et al., 2022) is a 16-item questionnaire aimed at measuring the frequency of use of primary coping strategies and the perception of coping self-efficacy. The Spanish version of the CSI-SF has demonstrated good internal consistency, as indicated by a Cronbach’s alpha of 0.86.- The Self Stigma Questionnaire (SSQ) (Ochoa et al., 2015) assesses self-stigma through 14 items and it has been validated in people with psychosis. The results for the Spanish version indicated good psychometric properties, with Cronbach’s alpha ranging between 0.75 and 0.90.

##### Cognitive functioning

2.3.1.6

- The Vocabulary subscale from Wechsler Adults Intelligence Scale (WAIS) (Wechsler, 2008) is used to explore premorbid intelligence quotient (IQ) in FEP (González-Blanch et al., 2011). It is a task based on an individual’s general knowledge of linguistic information (phonology and semantics), which has been generally associated with crystallized intelligence.- The Trail Making Test (TMTA-B) (Reitan, 1958; Sánchez-Cubillo et al., 2009) is a test integrating two parts: part A measures the speed of processing and part B measures mental flexibility. In each test the participant is asked to draw a line between 24 consecutive circles that are randomly arranged on a page. The TMT-A uses all numbers, whereas the TMT-B alternates numbers and letters, requiring the patient to switch between numbers and letters in consecutive order. The score represents the amount of time required to complete the task. The average for the TMT-B is 75 s, with deficiencies noted >273 s for the Spanish version.- The Screen for Cognitive Impairment in Psychiatry (SCIP) (Purdon, 2005; Pino et al., 2008) assesses cognitive difficulties in patients with severe psychiatric disorders. Spanish version showed an average time for administration of 16.02 (SD = 5.01) and an internal consistency Cronbach’s alpha value of 0.73.

##### Attachment and trauma

2.3.1.7

-The Psychosis Attachment Measure (PAM) (Berry et al., 2006; Sheinbaum et al., 2013) is a 16-item self-report scale designed to measure adult attachment in people with psychosis. For the Spanish version of the PAM, Cronbach’s alpha coefficients of 0.81 and 0.78 were found for the anxiety and avoidance subscales, respectively.-The Maltreatment and Abuse Chronology of Exposure Scale (MACE) (Teicher and Parigger, 2015) consists of 52 items that measures severity of exposure to ten types of maltreatment and provides an overall severity score and multiplicity score. Prior to this study, the MACE was adapted and translated into Spanish has been utilized in previous studies (Montoro et al., 2023).

#### Adolescents’ assessment

2.3.2

Adolescent children assessment includes the following instruments:

All adolescents complete a sociodemographic questionnaire.

##### Metacognitive and social cognition

2.3.2.1

Adolescents are assessed with the same battery of instruments as their mothers.

##### Clinical symptoms

2.3.2.2

-The Strengths and Difficulties Questionnaire (SDQ) (Goodman, 1997; Fonseca-Pedrero et al., 2011). The 25-item scale provides scores for 5 subscales including emotional symptoms, conduct problems, symptoms of hyperactivity/ inattention, peer problems, and prosocial behavior. In the Spanish version, Cronbach’s alpha ranged from 0.58 (behavioral problems) to 0.71 (emotional symptoms).

##### Social and familiar functioning

2.3.2.3

Adolescents are assessed with the with the FES as their mothers because it has been validated for the age population.

Satisfaction with Life Scale for Children and Adolecents (SWLS-N) (Diener et al., 1985; Sandín et al., 2015) is an age-downward version of the measure of life satisfaction developed by Diener. It is a 5-item, self-report instrument in which respondents are asked to indicate the degree to which t are satisfied each statement is true of their satisfaction with their life. The Spanish version of SWLS scale has demonstrated an alpha de Cronbach of 0.89 (García-Escalera et al., 2017).

The Children’s Global Assessment Scale (CGAS) (Shaffer, 1983) is an adaptation of the Global Assessment Scale (GAS) that assesses the level of functioning for a child or adolescent during a specified time period. It consists of a single score that ranges from 1 (most impaired) to 100 (healthiest). The CGAS has obtained good levels of reliability, with diagnostic agreement values between judges (kappa coefficient) higher than 0.90 (Santamarina-Perez et al., 2020).

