## Abstract

**Background:**

More than half of women with psychosis take care of their children despite the difficulties caused by the disease. Additionally, these kids have a higher risk of developing a mental health disorder. However, no interventions have been developed to meet these needs. Metacognitive Training (MCT) is a psychological intervention that has demonstrated its efficacy in improving cognitive insight, symptom management and social cognition in people with first-episode psychosis (FEP). Additionally, MCT has shown better results in women than men with FEP. This study aims to adapt and evaluate the efficacy of MCT-F in mothers and adolescent children in an online group context with the main purpose of improving family relationships, cognitive awareness and symptoms in women with psychosis and increase their children’s knowledge of the disease and their functioning. As secondary objectives, it also aims to evaluate improvements in metacognition, social cognition, symptoms, protective factors and self-perception of stigma.

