### Study aims

1.5

The objective of this study is to evaluate the efficacy of Family Metacognitive Training (MCT-F) in mothers with psychosis and adolescent children in an online group setting to improve family relationships, cognitive insight, symptoms of women with psychosis, and increase their children’s knowledge of the disease. As secondary objectives, we aim to evaluate improvements in metacognition and social cognition, symptoms, protective factors and self-perception of stigma. Finally, we aim to evaluate the feasibility and acceptability of MCT-F in both mothers with psychosis and their adolescent children.

We expect that MCT-F will be effective to improve cognitive insight in mother with psychosis as first hypothesis. As a secondary hypothesis we expect that MCT-F will improvement familiar functioning, metacognition and social cognition variables, as attributional style and Theory of mind, protective factors such as self-esteem, resilience and coping strategies and will decrease self-stigma in mothers. Regarding adolescent children’s participants, we hypothesize that MCT-F will increase children’s knowledge of their mothers’ disease and help them to better understand their mother’s thoughts and their understanding of metacognition and, consequently, to decrease anxiety and depressive symptoms. Furthermore, we expect an improvement in familiar functioning, metacognition and social cognition variables, as well as in protective factors such as: self-esteem, resilience, and coping strategies. More precisely, we expect that all outcomes’ measures will significantly improve from pre- to post-assessment and significant differences when compare with control evaluation. We will control the analysis by cognition functioning, previous trauma and attachment of the mother, presence of the illness before motherhood and attachment of the adolescent with their mother. Finally, we expected that MCT-F Twill be feasible and acceptable to both mothers and their adolescent children.

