### Data collection

2.4

Assessments are conducted at the three afore mentioned time points. Evaluators have been trained in psychological evaluation. The neuropsychological assessment will be carried out in the presence of the participants. The rest of the assessment will be conducted on another day and online to increase the feasibility and prevent fatigue due to the large number of assessment instruments. The assessment of the mother and the adolescent will be conducted separately but the same evaluator. Instruments used in each evaluation and the corresponding informant (mother or adolescent) is reported in Table 1. Types and dosages of the mothers’ medication as well as attendance to psychological and/or pharmacological treatment for the adolescent children will be recorded at the three time points of assessment.

**Table 1 tab1:** Measures used in the study with mothers and their adolescent children.

Instruments	Informants		Time of assessment		
	Mothers	Adolescent	T1	T2	T3
Inclusion/exclusion criteria	X	X	X		
Informed consent	X	X	X		
Sociodemographic and clinical questionnaire	X	X	X		
Clinical symptoms			X	X	X
PANSS	X		X	X	X
CDSS	X		X	X	X
SUMD	X		X	X	X
SDQ		X	X	X	X
Metacognition and social cognition					
BCIS	X	X	X	X	X
CBQ	X	X	X	X	X
JTC	X	X	X	X	X
AIHQ	X	X	X	X	X
The Hinting Task	X	X	X	X	X
Faces Test	X	X	X	X	X
SFRT-2	X	X	X	X	X
Familiar and social functioning					
FES	X		X	X	X
GAF	X	X	X	X	X
SWLS	X		X	X	X
CGAS		X	X	X	X
SWLS-N		X	X	X	X
Protective factors					
RSES	X	X	X	X	X
CD-RISC 10	X	X	X	X	X
CSI-SF	X	X	X	X	X
SSQ	X		X	X	X

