### Data analysis

2.7

The main analysis variable will involve the difference between scores in the control assessment and intervention assessment for the cognitive insight assessed in the mothers with psychosis. Secondary outcomes will be the changes in other assessments of metacognition and social cognition variables, familiar and social functioning, cognitive distortions, cognitive functioning, protective factors, and self-stigma.

The changes in the cognitive insight scales’ scores will be analyzed using repeated measures regression methods. Changes in the scores of symptoms, metacognition and social cognition, social functioning, understanding of the disease, self-esteem, resilience and coping strategies in adolescent children will be analyzed using repeated measures regression methods, with the final score of the scale as the dependent variable. Two additional analyses will be carried out to examine the robustness of the results. First, the intention-to-treat analysis will be performed after replacing missing values for the dropout cases using the method “last observation carried forward” (LOCF). Next, the analyses will be performed only with data from participants who complete the treatment and who have been evaluated at both time points. Finally, the satisfaction of patients undergoing group treatment will also be analyzed.

All the analyses will be controlled by medication changes, cognitive functioning, attachment, trauma, start of the illness before motherhood and type of TAU (in mothers), and the presence of mental disorders or attendance to psychological and/or pharmacological treatment (in adolescents).

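### The text gives adolescents the FES but Table 1 schedules it for mothers only; if the table is followed, the adolescent family-functioning hypothesis has no repeated measure

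*Protocol article*

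**What the plan says.** Section 2.3.2.3, on the adolescents' instruments, is explicit: "Adolescents are assessed with the with the FES as their mothers because it has been validated for the age population". It then lists two further instruments for them, the SWLS-N and the CGAS. It does not list the GAF, which section 2.3.1.4 describes among the mothers' instruments.

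Section 2.4 gives Table 1 its authority: "Instruments used in each evaluation and the corresponding informant (mother or adolescent) is reported in Table 1". In the block headed "Familiar and social functioning", the FES row has a mark under mothers, none under adolescents, and marks at T1, T2 and T3. The GAF row has marks under both informants at all three times.

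Section 2.3.1.4 says of the FES: "This questionnaire assesses interpersonal relationships between family members". Family relationships belong to the overall purpose in the abstract ("with the main purpose of improving family relationships, cognitive awareness and symptoms in women with psychosis") and to the objective in section 1.5 ("to improve family relationships, cognitive insight, symptoms of women with psychosis"). For the adolescents in particular, section 1.5 adds: "we expect an improvement in familiar functioning, metacognition and social cognition variables".

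Section 2.7 names familiar as well as social functioning in its general sentence on secondary outcomes. Its sentence on the adolescents begins "Changes in the scores of symptoms, metacognition and social cognition, social functioning, understanding of the disease" and goes on to self-esteem, resilience and coping. Family functioning is not in that list.

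**The concern.** The article gives two incompatible instructions about one questionnaire in one group of participants. The table is the part that an evaluator is most likely to work from, because the text sends the reader there to learn the informant for each instrument.

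At stake is a stated adolescent hypothesis. The design uses each participant as their own control, comparing change over the 11 weeks without intervention with change over the intervention. A questionnaire not given at T1 or T2 cannot be collected afterwards, and no later analysis plan can restore it. The adolescent-specific sentence in section 2.7 does not settle the matter, since it leaves family functioning out.

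**Working it through.** No figure in the plan depends on this point, so there is nothing to recompute. The check sets the text against the table and asks what remains under each reading.

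**Step 1: is the table row intact?** The marks in the relevant block of Table 1, compared with the text of sections 2.3.1.4 and 2.3.2.3:

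| Instrument | Table: mothers | Table: adolescents | Table: times | Text: adolescents |
|---|---|---|---|---|
| FES | yes | no | T1, T2, T3 | **yes** |
| GAF | yes | **yes** | T1, T2, T3 | not listed |
| SWLS | yes | no | T1, T2, T3 | no (SWLS-N instead) |
| CGAS | no | yes | T1, T2, T3 | yes |
| SWLS-N | no | yes | T1, T2, T3 | yes |

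The FES row has the same pattern as mothers-only rows such as the SWLS and SSQ. Instruments given to both groups elsewhere in the table (BCIS, RSES, CD-RISC 10) carry two informant marks, and adolescent-only rows carry theirs in the second column. The row therefore reads as intact, and the mismatch is not a product of text extraction. Two of the five rows disagree with the text, and they are adjacent.

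**Step 2: what does the own-control contrast need?** With Y1, Y2 and Y3 the scores at T1, T2 and T3, the natural contrast is

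D = (Y3 − Y2) − (Y2 − Y1) = Y3 − 2·Y2 + Y1,

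which needs all three scores.

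**Step 3: what is available for adolescents' family functioning?**

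- Following section 2.3.2.3: FES at T1, T2 and T3. Three scores per adolescent on each of cohesion, expressiveness and conflict; D can be formed.
- Following Table 1: no FES scores; D cannot be formed.
- CaMir-R: section 2.3.2.5 says that it draws partly on family functioning, but Table 1 gives it at T1 only. One score, so neither Y2 − Y1 nor Y3 − Y2 exists.
- The other repeated adolescent instruments in the block rate general functioning (CGAS, and the GAF as marked) or life satisfaction (SWLS-N). None is described as a measure of family relationships.

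**Step 4: what is untouched?** The mothers' FES is scheduled at all three times under either reading. The primary outcome, mothers' cognitive insight, and the sample size of 48 mothers do not involve the adolescent FES.

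**The case against.** The strongest reply is that this is a slip in a journal table. The text is explicit and gives a reason for using the FES in this age group, and the unsupported GAF mark directly below the blank FES cell looks like a mark put in the wrong row. The full protocol and the case report forms are not shown, so it is not known that any evaluator works from this table. That stands as a limit: the loss is conditional, and a misplaced mark is plausible though not confirmed. It does not remove the contradiction, because the article itself makes the table the reference for informants.

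Several stronger readings are tempting, and the documents do not support them:

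- *Adolescents would contribute no data at all on family matters.* The CaMir-R at T1 covers perceived family functioning. What would be missing is a repeated measure.
- *A main aim would go unmeasured, or would lose half of its evidence.* Mothers' FES data are collected under either reading, and no source gives the adolescents' share of the evidence. What the abstract and section 1.5 single out for the children is chiefly knowledge of the disease; family functioning is a further hypothesis for them.
- *At least 48 adolescents would lose scores at all three visits.* The 48 is the number of mothers after allowing for 25% losses, so about 48 × 0.75 = 36 mothers would be expected to remain. Each mother may bring more than one child, so the number of adolescents is not fixed.
- *Section 2.7 ignores family functioning.* Its general sentence on secondary outcomes includes it and is not expressly limited to mothers. Only the adolescent-specific list omits it.
- *The adolescent GAF mark is an error and should be deleted.* The text does not list the GAF for adolescents, but participants may be up to 20 years old and the CGAS is described as a scale for a child or adolescent. The documents do not say whether the mark is intended.

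**Conclusion.** The point holds as an internal contradiction that needs correction. Section 2.3.2.3 and Table 1 disagree on whether adolescents complete the FES, and they also disagree on the GAF.

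The size depends on which version is used. If evaluators follow the text, the harm is a misreported schedule. If they follow the table, adolescent FES assessments fall from three to none, and the adolescent family-functioning hypothesis in section 1.5 cannot be tested with the own-control contrast. The article does not show which version is in use. This conclusion assumes that Table 1 as printed is the table that the authors intended to publish and that no other repeated adolescent measure of family functioning exists outside the article.

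**What to change.** 1. In Table 1, mark the FES for adolescents, so that T1, T2 and T3 apply to them as section 2.3.2.3 states.
2. Reconcile the adolescent mark in the GAF row with section 2.3.2.3: say whether it is intended, and for whom, or is an error.
3. In section 2.7, name family functioning (FES) in the adolescent outcome list, in line with the general secondary-outcome sentence there.
4. Confirm which version the evaluators have been using. If it was the table, report from which assessment the adolescent FES was added.

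The cost is one or two informant marks and one sentence. There is no burden beyond what the text already promises, a 30-item true/false form. The correction is worth most if made before further T1 and T2 assessments pass, since those cannot be recovered.

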##### Protective factors

2.3.2.4

Adolescents are assessed with the same battery of instruments as their mothers. These instruments have been validated for the age population, except for the Self-Stigma Questionnaire (SSQ), which is not administered.

##### Attachment

2.3.2.5

- The short version of Cartes, Modèles Indivuels de Relation (CaMir-R) (Balluerka et al., 2011) is a questionnaire aimed at measuring attachment cognitions. It is based on the subjects’ evaluations of past and present attachment experiences and family functioning. The Spanish version of the CaMir-R has demonstrated good internal consistency, as indicated by a Cronbach’s alpha of 0.81.

##### Cognitive functioning

2.3.2.6

- The Vocabulary subscale from Wechsler Adults Intelligence Scale (WAIS) (Wechsler, 2008) is used to explore the premorbid intelligence quotient (IQ) in adolescents aged 16 years or older. For those participants younger than 16, the Vocabulary subscale of the Wechsler Intelligence Scale for Children (Wechsler, 2014) is used.- The Matrix Reasoning Task of the Wechsler Intelligence Scale for Children (Wechsler, 2008, 2014) measures visual processing and abstract, spatial perception.- The Trail Making Test (TMTA-B) (Reitan, 1958; Sánchez-Cubillo et al., 2009) is applied using scales from the age range of the study.

##### Feasibility and acceptability

2.3.2.7

All mothers and adolescent’s participants are also asked about the perceived value and usefulness of the intervention and the delivery format through a brief self-reported questionnaire divided into two parts. The first part consists of 8 generic items on an 11-point Likert scale from 0 (“not at all”) to 10 (“completely”). The second part consists of 8 short open-ended questions. Finally, we will evaluate the impact of the program’s aim to increase adolescent children’s knowledge of their mothers’ disease with the following items: “To what extent do you feel you understand your mom’s disease before participating in the training?” and “To what extent do you feel you understand your mom’s disease after participating in the training?” with Likert-type response options (from 0 “Not at all” to 5 “Completely”).

In addition, after each session participants are asked to answer two questions to measure the perceived usefulness and enjoyment of each module: “How much did you enjoy it?” and “How useful did you find it?”

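### Adolescents' understanding of the mother's illness, a main aim, has no control-period measurement, so the own-control comparison expected of every outcome cannot be made for it

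*Protocol article*

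**What the plan says.** **Aim.** The main objective in section 1.5 covers family relationships, cognitive insight, "symptoms of women with psychosis, and increase their children’s knowledge of the disease". The secondary objectives follow in a separate sentence. The Background of the Abstract likewise includes in the main purpose to "increase their children’s knowledge of the disease and their functioning".

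**Measure.** Section 2.3.2.7 (Feasibility and acceptability) states: "we will evaluate the impact of the program’s aim to increase adolescent children’s knowledge of their mothers’ disease with the following items". Two self-ratings follow, each from 0 to 5. One asks how far the adolescent feels they understand the mother's "disease before participating in the training", the other her "disease after participating in the training".

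**Schedule.** In Table 1 the feasibility and acceptability row is marked for mothers and adolescents at T3 only. A footnote extends that row to the training sessions. Section 2.3.2.7 describes the per-session questions as covering enjoyment and usefulness of each module.

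**Analysis.** Section 2.7 says that changes in several scores, including "understanding of the disease, self-esteem, resilience and coping strategies in adolescent children will be analyzed using repeated measures regression methods". Section 1.5 expects all outcome measures to improve from pre to post and to show "significant differences when compare with control evaluation".

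**The concern.** The trial has no parallel comparison group. Its control is the 11-week period without intervention between T1 and T2, and the limitations paragraph of the Discussion relies on participants acting as their own control to offset the missing group. An outcome shares that protection only if it is measured at T1 and T2. Understanding of the disease appears not to be, yet it is a stated main aim and is listed for the same type of analysis as outcomes that are measured three times.

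The risk is that a before/after difference on this pair is reported as an effect of the training. Nothing in the data would separate learning from change that would have occurred anyway or, if the before-rating is recalled, from a change in how the adolescent judges their earlier state.

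**Working it through.** No figure in the plan has to be reproduced. The check sets the aim, measure, schedule and analysis side by side.

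**Step 1. Is there another measure?** No other row of Table 1 measures knowledge or understanding of the disease. The per-session questions do not ask about it, and the sessions all fall after T2, so the footnote adds no T1 or T2 value.

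**Step 2. Count the scheduled values, under two readings of when the before-item is asked.**

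| Reading | T1 | T2 | T3 |
|---|---|---|---|
| A. Both items at T3, as Table 1 implies | none | none | after-rating, plus recalled before-rating |
| B. Before-item asked just before session 1 | none | prospective rating | after-rating |

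**Step 3. Compare with what the own-control comparison needs.** Written as a contrast of the two periods, it is

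(T3 − T2) − (T2 − T1).

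- Reading A: T2 − T1 does not exist, and T3 − T2 has no prospective baseline.
- Reading B: T3 − T2 exists, but T2 − T1 still does not.

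Under both readings the contrast cannot be estimated for any adolescent. An analysis plan cannot supply this, because the data are not collected.

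**Step 4. What the pair does estimate under reading A.** Let U₀ be the rating the adolescent would have given before training, R the same rating as recalled at T3, and U₁ the after-rating. Then

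reported gain = U₁ − R = (U₁ − U₀) + (U₀ − R).

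The first term is the change in self-rated understanding; the second is the recall or response shift. The shift enters the reported gain one for one, and the pair cannot separate the two terms. The documents give neither the size nor the direction of U₀ − R. Under reading B this term disappears, but U₁ − U₀ remains an uncontrolled before/after change.

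**Step 5. What is being rated.** Both items ask how far the adolescent feels they understand. They measure perceived understanding, and there is no separate test of knowledge.

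**The case against.** The case for a milder view has several parts.

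- **Timing is inferred.** Section 2.3.2.7 does not say when the before-item is asked. The T3 reading rests on Table 1, which is not wholly reliable: it marks the FES for mothers only, although section 2.3.2.3 gives it to adolescents too; it marks the GAF for adolescents, although the text gives them the CGAS; and its legend defines a trauma questionnaire that has no row. This stands. T3 is the likeliest timing but not a certain one. The missing T1 value does not depend on it.
- **The pair can be analysed.** Two ratings per person can be fitted as a within-person factor or compared as a pair, and section 2.7 does not state the number of time points for adolescents. A reader might infer that no repeated-measures analysis is possible. That goes too far; only the comparison with the control period is impossible.
- **The control comparison comes from a hypothesis.** Section 2.7 spells out the control-versus-intervention difference for mothers' cognitive insight. The extension to all outcomes is in section 1.5. This is fair, but section 1.5 does say all, and no exception is made for this outcome.
- **The bias is not quantified.** A reader might infer that the two items are shown side by side after 11 sessions spent teaching the illness, and that the gain must therefore be inflated. The documents do not support this. They give no layout for the items. Section 2.5 describes one added psychoeducation session on the illness, with the other sessions on cognitive biases, on depression, self-esteem and self-stigma, and on separate discussion. They also say nothing on the direction or size of any recall shift.
- **The outcome is not primary.** The primary outcome and the sample size concern mothers' cognitive insight, and the Discussion calls the study a pilot. This stands and limits the weight of the point.

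**Conclusion.** The point holds as an inconsistency between aim, schedule and analysis for one outcome. Understanding of the disease is named among the main aims, has no T1 value, and on the likeliest reading has no prospective T2 value. The comparison with the control period is therefore unavailable for all adolescents. What remains is an uncontrolled before/after difference in self-rated understanding, probably with a recalled baseline and so open to recall and response-shift bias of unknown size.

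The missing control comparison rests only on Table 1 and section 2.3.2.7 offering no T1 measurement. The recall concern rests on the further assumption that the before-item is asked at T3.

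This should be corrected, but it does not threaten the trial's main result. A reader might infer that the primary analysis is compromised; it is not, because the BCIS is scheduled at T1, T2 and T3.

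**What to change.** 1. Ask adolescents one item on how well they understand their mother's disease now (0-5), in identical wording at T1, T2 and T3. Add it as a row in Table 1.
2. Analyse that item with the same control-versus-intervention-period contrast as the other outcomes.
3. Keep the before/after pair as an acceptability item, and state in section 2.3.2.7 when each of its two questions is asked.
4. For adolescents already past T1 or T2, report the pair descriptively as uncontrolled perceived change, take it out of the control comparison in sections 1.5 and 2.7, and make no efficacy claim on knowledge from it. Section 2.1 gives recruitment as March to May 2024, so this may apply to many or all of them.

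The cost is one extra item at two existing assessments (T3 already carries an almost identical rating), a line in Table 1 and a short amendment. For those already assessed, the cost is a weaker stated conclusion on this aim.
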